## Methods and Analysis

### Study Design

This is a multi-center, double-blind, randomized controlled trial, which will be conducted in Yueyang Hospital of Integrated Traditional Chinese and Western Medicine Affiliated to Shanghai University of Traditional Chinese Medicine, Shanghai Pulmonary Hospital Affiliated to Tongji University, Shanghai Chest Hospital Affiliated to Shanghai Jiaotong University, Guang’anmen Hospital of China Academy of Chinese Medical Sciences, First Affiliated Hospital of Guangzhou University of Traditional Chinese Medicine, First Affiliated Hospital of Tianjin University of Traditional Chinese Medicine, Affiliated Hospital of Chengdu University of Traditional Chinese Medicine, and Jiangsu Provincial Hospital of Traditional Chinese Medicine. The study aims to enroll 314 advanced NSCLC patients with EGFR mutation-positive. Patients will be randomized at a ratio of 1:1 to receive either osimertinib plus YYJD or osimertinib plus placebo. Follow-up will be conducted at baseline, 4 weeks after treatment, and every 8 weeks afterward until disease progression or death, which is evaluated according to Response Evaluation Criteria in Solid Tumors (RECIST) version 1.1. The study design is based on the Standard Protocol Items: Recommendations for Interventional Trials (SPIRIT) 2013 statement (Chan et al., 2013). The flow diagram of the study is shown in Figure 1.

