### Outcomes

Computed tomography (CT) or magnetic resonance (MR) imaging will be used to assess the tumor at baseline, 4 weeks after treatment, and every 8 weeks afterward until disease progression or death. Objective response is evaluated according to RECIST 1.1, established by the National Cancer Institute (NCI), and divided into the following four situations: Complete Response (CR), Partial Response (PR), Stable Disease (SD), and Progressive Disease (PD).

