#### Secondary Outcomes

(1) Overall survival (OS): calculated as the time from randomization to death due to any cause. For subjects who are lost to follow-up before death, the time of the last follow-up is used as the time of no death.(2) Objective response rate (ORR): calculated based on the effective rate of CR+PR patients.(3) Disease control rate (DCR): calculated based on the effective rate of CR+PR+SD patients.(4) Physical condition: assessed following the ECOG PS standard at the same time point of image evaluation.(5) QoL: evaluated with Functional Assessment of Cancer Therapy-Lung (FACT-L) questionnaire, Lung Cancer Symptom Scale (LCSS) and TCM syndrome score at the same time point of image evaluation. TCM syndrome score will be evaluated based on the grading scales of lung cancer symptoms required in the Guiding Principles of Clinical Research of New Chinese Medicine Treating Primary Bronchial Lung Cancer (2002 Edition) issued by the National Medical Products Administration of China.(6) Safety assessments: Participants will be asked and all adverse events (AEs) during treatment will be recorded at each visit, and all AEs reported will be analyzed. Blood, urine, and stool routine, liver function, and kidney function are tested for adverse reactions at the same time point of image evaluation and evaluated according to common terminology criteria for adverse events (CTCAE) version 5.0 (https://ctep.cancer.gov).

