### Statistical Analysis

Data analysis will follow the trial’s statistical analysis plan. All data will be processed by statistical analysis with SAS 9.4 software analysis. Two-tailed *p* values <0.05 are considered statistically significant. The analysis will follow intention-to-treat, full analysis set, and per-protocol subject principles for the evaluation of primary and secondary outcomes. The safety data set that includes all subjects who received at least one treatment after randomization will be used to evaluate safety and tolerance. Missing data will be processed with the multiple imputation method.

The baseline characteristics will be reported according to treatment groups. PFS and OS will be illustrated by the Kaplan–Meier survival curve and compared between groups using the log-rank test. The secondary outcomes will be summarized with frequency, mean, standard deviation, median, and range. At each time point, comparisons between the experimental group and the placebo group will be conducted using the Group t-test or Wilcoxon rank-sum test (for measurement data) and the rank-sum test and CMH test (for count data). Fisher’s exact test will be used to compare tumor response rates between the arms. For PFS, an adjusted Cox regression model will be used to estimate the adjusted HRs for differences between the treatment arms with the selected prognostic factors, including the center, EGFR mutation type, age, sex, EGFR-TKI drugs, smoking status, and ECOG PS.

Safety will be documented in adverse event forms and presented with descriptive statistics for each group. The frequency difference of adverse events between groups will be assessed by the chi-square test or Fisher’s exact test. For different AE severities, a rank-sum test will be performed to analyze the independent ordered multiple category data between the two groups.

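### FACT-L, LCSS, TCM score and ECOG PS are compared visit by visit with two-sample tests at 0.05, with no stated use of baseline, repeated measures or a summary contrast

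*Protocol article*

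**What the plan says.** The Secondary Outcomes section ties four measures to the imaging visits. Quality of life is "evaluated with Functional Assessment of Cancer Therapy-Lung (FACT-L) questionnaire, Lung Cancer Symptom Scale (LCSS) and TCM syndrome score at the same time point of image" (that is, at each scan), and physical condition is "assessed following the ECOG PS standard at the same time point of image evaluation". The Outcomes section gives the imaging calendar: "assess the tumor at baseline, 4 weeks after treatment, and every 8 weeks afterward until disease progression or death". Study Design gives the same calendar for follow-up.

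The Statistical Analysis section then fixes how the arms are compared: "At each time point, comparisons between the experimental group and the placebo group will be conducted using the Group t-test or Wilcoxon rank-sum test". That rule applies to outcomes treated as measurements. A different pair of methods is named where the outcome is categorical, namely "the rank-sum test and CMH test (for count data"). The threshold is general: "Two-tailed *p* values <0.05 are considered statistically significant". Covariate adjustment is described for PFS only. On incomplete data there is one sentence: "Missing data will be processed with the multiple imputation method".

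The section refers to a separate statistical analysis plan, which is not at hand.

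**The concern.** The per-visit test is a method the article states, so an unseen analysis plan would have to depart from the published text to change it. It has three weaknesses.

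- **Multiplicity without a summary.** Each scale yields a string of p-values and no single treatment effect. No visit or scale leads, so a few significant visits could be read as a quality-of-life benefit.
- **Information not used.** A baseline score is collected and each patient contributes several scores, yet each test as described uses one visit at a time.
- **Shrinking comparison groups.** Assessment ends at progression or death, so a later visit compares only those who remain. If YYJD prolongs PFS as planned, the arms lose patients at different rates and the comparison is no longer between the groups as randomised.

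Quality of life is named among the secondary outcomes in the abstract, so readers will look at these results.

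**Working it through.** The article gives no number of tests, so there is no figure of its own to reproduce here.

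**Inputs.** Visits at week 4 and every 8 weeks after that (Study Design, Outcomes); four measures (Secondary Outcomes); 30 months in total with 18 months of recruitment, median PFS 18 and 23 months, 1% censoring per month and 157 patients per arm (Sample Size); alpha 0.05 two-tailed (Statistical Analysis). Assumptions: exponential PFS, uniform accrual, and the correlations named below.

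**Number of tests.** 30 months is about 130 weeks. Visits fall at weeks 4, 12, ..., 124: (124 − 4)/8 + 1 = 16. With four measures, 16 × 4 = 64 tests. To week 52: (52 − 4)/8 + 1 = 7 visits, 7 × 4 = 28 tests.

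**False positives if there is no effect.** Expected number: 64 × 0.05 = 3.2, and 28 × 0.05 = 1.4. These hold whatever the correlation between tests. Chance of at least one:

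| Case | 64 tests | 28 tests |
|---|---|---|
| Independent tests, 1 − 0.95^n | 96% | 76% |
| Simulated, between-scale correlation 0.3–0.7, between-visit 0.5–0.7 (assumed) | about 56–93% | not run |

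**Progressed or died, at the planned medians**, 1 − 0.5^(t/median):

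| Month | Control (18 months) | YYJD (23 months) |
|---|---|---|
| 12 | 1 − 0.5^(12/18) = 37% | 1 − 0.5^(12/23) = 30% |
| 24 | 1 − 0.5^(24/18) = 60% | 1 − 0.5^(24/23) = 51% |

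**Patients still assessed.** 157 × (share enrolled early enough to reach the visit) × exp[−(ln 2/median + 0.01) × t]:

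| Week | Control | YYJD |
|---|---|---|
| 52 | 88 | 97 |
| 100 | 20 | 24 |
| 124 | 3 | 4 |

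With 3 against 4 patients there are 35 possible rank allocations, so the smallest two-sided exact rank-sum p-value is 2/35 = 0.057. That visit cannot reach 0.05 on the rank test.

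**Value of the baseline.** Adjustment multiplies the variance by 1 − r². The detectable difference at 80% power with all 157 per arm assessed is (1.960 + 0.842) × √(2/157) = 0.316 SD unadjusted, and this times √(1 − r²) when adjusted:

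| Assumed r | Variance factor | Reduction | Detectable difference |
|---|---|---|---|
| 0.3 | 0.91 | 9% | 0.302 SD |
| 0.5 | 0.75 | 25% | 0.274 SD |
| 0.7 | 0.51 | 49% | 0.226 SD |

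**The case against.** These are secondary outcomes, the article nowhere calls the per-visit p-values confirmatory, and a condensed article may leave the lead scale, key visit and multiplicity rule to the analysis plan. That is fair, and their absence alone would be no finding. What remains is the stated method.

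The measurement data might be changes from baseline, and a CMH test can be stratified. Neither is stated, so the accurate claim is that no use of baseline is described, not that it is deliberately discarded. Change scores would still leave separate tests at every visit.

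The count of 64 is a ceiling. It assumes all four measures are tested at all 16 visits, although very few patients reach the last ones. The 96% is likewise an upper figure that requires independence. A reader might infer that chance findings are near certain, but with correlated visits and scales the assumed range goes down to about 56%.

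A reader might also infer that scores will be imputed after progression or death. The article does not say so. Assessment ends there by design, so later scores need not count as missing. The sentence on imputation simply does not mark its limits. Nor does it contradict the OS definition: patients lost before death have their own censoring rule, a censored time is not a missing value, and nothing says survival times are imputed.

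Finally, a mixed model is no complete cure. It relies on data being missing at random and implicitly extrapolates scores for patients who have progressed or died. That objection stands, and the fix has to deal with it.

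**Conclusion.** The point holds as a weakness of a stated method. Per-visit two-sample tests give up to 64 comparisons by month 30, of which 28 fall by week 52, with 3.2 and 1.4 false positives expected if there is no effect. At least one is likely rather than certain: about 56–93% for the 64 tests under the assumed correlations. The unequal depletion is moderate, 7 percentage points at month 12 and 9 at month 24, and depends on the planned medians and exponential PFS. The documents do not show which way it would bias a late-visit comparison. The precision gained from baseline adjustment depends wholly on an unknown correlation.

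The documents do not support saying that the plan imputes beyond progression or death, or that its imputation rule conflicts with OS censoring. On both, only a clarification is needed. The primary PFS conclusion is unaffected. The change should be made, but the trial's main result does not depend on it.

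**What to change.** 1. For FACT-L, LCSS and TCM score, replace the per-visit tests with one repeated-measures model per scale: baseline score, treatment, visit, treatment-by-visit, and the randomisation factors sex, age group and centre.
2. Name one lead scale, such as FACT-L total, and one contrast over early visits while most patients are still assessed, for example the average over the 7 visits to month 12. Naming a lead matters: four contrasts each at 0.05 would still give 1 − 0.95^4 = 18.5% if independent.
3. For ECOG PS, a short ordered grade, use an ordinal model adjusted for baseline.
4. Show the other visits descriptively with confidence intervals and numbers assessed.
5. State that the estimate concerns patients while alive and progression-free, or add a sensitivity analysis for dropout at progression or death. Without one of these, the mixed model extrapolates past those events under missing-at-random.
6. Clarify that multiple imputation covers only questionnaires missed while assessment was still scheduled, and that PFS and OS are handled by censoring.

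The cost is analysis-plan wording and standard SAS code. No new data are needed, and the change should be made while allocation is still concealed. What is given up is the set of per-visit p-values.

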#### Inclusion Criteria

(1) Pathologically confirmed NSCLC (Health Commission of PRC and National Health Commission of the People’s Republic of China, 2019).(2) Locally advanced or metastatic NSCLC that is not amenable to curative surgery or radiotherapy.(3) The tumor has one of 2 common EGFR mutations known to be associated with EGFR-TKI sensitivity (Ex19del, L858R).(4) Patients must have no treatment for locally advanced or metastatic NSCLC.(5) Aged 18–74 years old.(6) No major organ dysfunction: hemoglobin ≥120 g/L, absolute neutrophil count (ANC) ≥1.5 × 10^9^/L, platelets ≥80 × 10^9^/L, bilirubin ≤ 1.5ULN, alkaline phosphatase (AP), aspartate aminotransferase (AST), and alanine aminotransferase (ALT) ≤ 2.5 × ULN. INR ≤ 1.5, creatinine ≤ 1.5 × ULN.(7) Provision of informed consent forms.

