#### Exclusion Criteria

(1) Those with a history of other malignancies within 5 years;(2) Those with symptomatic brain metastases;(3) Those with congestive heart failure (> class II NYHA heart function), unstable (angina at rest), initial onset (starting within 3 months), angina pectoris, or myocardial infarction occurring within 6 months;(4) Those with active infection (> Grade 2 adverse events according to CTCAE.5.0 version);(5) Those with a history of uncontrollable mental illness.

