### Randomization

Eligible patients enrolled at each site will be randomly allocated to either the O+YYJD group or the O+placebo group at a 1:1 ratio through a dynamic random method. When patient gender (male vs. female), age (≥65 years old vs. <65 years old), and enrollment center is input as stratified factors, the software will automatically output the results of randomization. Personnel for drug administration will be able to obtain a random number and group allocation immediately in the form of a short message service and complete drug distribution according to the allocation.

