### Interventions

Patients in the O+YYJD group will receive osimertinib and YYJD granule. Patients in the O+placebo group will receive osimertinib and placebo.

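### The Cox covariates named for PFS leave out disease stage and baseline brain metastases, on which eligible patients differ, and include an EGFR-TKI drug term that is constant; the cost is modest and the correction almost free

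*Protocol article*

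**What the plan says.** All places are in the protocol article.

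- **Statistical Analysis, Cox model.** An adjusted Cox model for PFS uses selected prognostic factors, "including the center, EGFR mutation type, age, sex, EGFR-TKI drugs, smoking status, and ECOG PS". This is the only analysis in the section that is said to give a hazard ratio.
- **Statistical Analysis, test.** PFS and OS are "illustrated by the Kaplan–Meier survival curve and compared between groups using the log-rank test". No stratification is stated.
- **Randomization.** The dynamic allocation uses "patient gender (male vs. female), age (≥65 years old vs. <65 years old), and enrollment center is input as stratified factors".
- **Inclusion Criteria.** Disease extent may be "Locally advanced or metastatic NSCLC that is not amenable to curative surgery or radiotherapy".
- **Exclusion Criteria.** The only exclusion on brain involvement is "Those with symptomatic brain metastases", so patients with asymptomatic brain metastases can enter.
- **Interventions.** "Patients in the O+YYJD group will receive osimertinib and YYJD granule. Patients in the O+placebo group will receive osimertinib and placebo".

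The Statistical Analysis section also says that the analysis follows a separate statistical analysis plan, which is not shown.

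**The concern.** Disease extent differs between eligible patients in two ways, stage and brain metastases. Neither is balanced by the allocation or named for adjustment. If the arms differ on either by chance, the planned hazard ratio carries that difference, except for whatever part ECOG PS picks up.

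The list also does not look fitted to this trial. A term for the EGFR-TKI drug would vary in the previous CATLA study, which the Introduction says used gefitinib, erlotinib or icotinib. Here it is constant and adjusts for nothing. A list that holds a constant and lacks disease extent is poorly fixed. If the list is meant to be open, covariates could be chosen after an imbalance has been seen.

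At stake is the precision of the main PFS estimate and how well its covariates are pre-specified. The validity of the comparison is not at stake.

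**Working it through.** **Lists side by side**

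| Factor | Varies under eligibility | Used in allocation | Named in Cox model |
|---|---|---|---|
| Sex, age, center | yes | yes | yes |
| EGFR mutation type | yes | no | yes |
| Stage (locally advanced / metastatic) | yes | no | no |
| Brain metastases (asymptomatic) | yes | no | no |
| EGFR-TKI drug | no | no | yes |

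**Expected events and standard error**

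Inputs from Sample Size: medians 18 and 23 months, 157 per arm, 18 months of recruitment, 30 months in total, 1% censoring per month. With exponential PFS the design HR is 18/23 = 0.783, log HR -0.245. With uniform accrual the event probability is 0.498 in the control arm and 0.420 in the YYJD arm. Events are 157 × (0.498 + 0.420) ≈ 144, so the standard error of the log HR is about 2/√144 = 0.167.

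The article's total of 314 does not reproduce from these inputs. HR 0.783 at two-sided 0.05 and 80% power needs 523 events (Schoenfeld), while 144 events give about 31% power. That is a separate and much larger matter. It enters here only because the power figures below start near 30%.

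**Size of a chance imbalance**

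The documents give neither the prevalence p nor the prognostic HR of either factor. Assumed ranges: p = 20-40%, factor HR = 1.3-2.0.

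- SD of the difference in proportions between arms = √(2p(1−p)/157): 4.5 points at p = 20%, 5.2 at 30%, 5.5 at 40%.
- 95% limit = 1.96 × SD: 8.8, 10.1 and 10.8 points.
- Shift in log HR ≈ ln(factor HR) × imbalance.

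Factor by which the PFS HR moves at the 95% limit:

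| Prevalence | Factor HR 1.3 | Factor HR 1.5 | Factor HR 2.0 |
|---|---|---|---|
| 20% | 1.023 | 1.037 | 1.063 |
| 30% | 1.027 | 1.042 | 1.073 |
| 40% | 1.029 | 1.045 | 1.078 |

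The SD that the omitted factor adds to the log HR is 0.01 to 0.04, against the total standard error of about 0.167. The 95% confidence limits themselves lie a factor of exp(1.96 × 0.167) ≈ 1.39 from the estimate.

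**Simulation: 157 per arm, 30% prevalence, 1,500 trials per scenario**

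| True HR | Factor HR | Rejection without / with factor | Mean HR without / with factor |
|---|---|---|---|
| 1.0 | 1.5 | 3.7% / 3.8% | 0.993 / 0.994 |
| 1.0 | 2.0 | 4.8% / 4.9% | 0.992 / 0.994 |
| 0.783 | 1.5 | 30.1% / 30.5% | 0.786 / 0.783 |
| 0.783 | 2.0 | 29.7% / 31.1% | 0.786 / 0.779 |

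Adding the factor leaves the type I error unchanged. At the design effect, power rises by 0.4 to 1.4 points. The average pull of the HR toward 1 is under 1% (0.786/0.779 = 1.009).

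A second set, with 3,000 trials per scenario and a mutation-type effect of HR 1.4 also assumed, gave power of 31.1% to 31.9% (factor HR 1.5) and 28.8% to 31.3% (factor HR 2.0). Those are gains of 0.8 and 2.5 points. Across both sets the gain is 0.4 to 2.5 points.

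**The case against.** The strongest reply is that nothing here is stated wrongly. The covariates are introduced as examples of selected factors, the analysis plan is not shown, and the final covariate set is commonly left to that plan. This stands in part: it cannot be confirmed that stage and brain metastases are finally left out. But the article does name a list, and one named item cannot work in this trial, so the list needs correcting in any case.

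The second reply is that the harm is small and rests on outside inputs. This stands. No passage gives the prevalence or prognostic weight of either factor. The simulations treated a single binary factor at 30% prevalence, and stage was not simulated separately. Nor does the article show that every asymptomatic patient has brain imaging at baseline: it specifies only CT or MR to assess the tumor, and the schedule figure is not shown.

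A reader might go further and infer three things that the documents do not support.

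- **That the PFS comparison is biased.** Chance imbalance after randomisation is random error, already covered by the test and the confidence interval. The simulated type I error bears this out.
- **That an HR of 0.81-0.84 in place of 0.78 is to be expected.** That range was seen only in simulated trials with an 8-12 point excess in the YYJD arm. At 30% prevalence such an excess occurs in about 5% of trials, and the mirror image is as likely.
- **That EGFR mutation type has the same gap.** It is missing from allocation but named in the Cox model, so the adjusted HR already corrects for it.

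**Conclusion.** The point holds as a minor, low-cost improvement. The named Cox covariates omit stage and baseline brain metastases although eligible patients differ on both and allocation balances neither, and they include a term that is constant here.

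The size is a shift in the PFS HR by a factor of about 1.02 to 1.08 at the 95% limit of imbalance, and a power gain of roughly 0.4 to 2.5 points at the design effect. The shift assumes 20-40% prevalence and a factor HR of 1.3-2.0. The power figures assume 30% and 1.5-2.0. ECOG PS may already absorb part of the effect, which would make both smaller.

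The material does not support a claim of bias or an inflated type I error. It also does not support a change to the running allocation.

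**What to change.** Before unblinding, amend the covariate list in Statistical Analysis, and in the analysis plan if it repeats the list:

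- remove the EGFR-TKI drug term;
- add stage (locally advanced / metastatic);
- add brain metastases at baseline (yes/no, as recorded at baseline), with a stated rule for patients in whom this was not recorded;
- state that the list is closed.

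Since brain metastases imply metastatic disease, the two additions amount to one three-level factor.

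The change needs no more patients and, because brain metastases are used as recorded, no new procedure. It uses two more model parameters, while the removed term contributed none. With about 144 events, eight centers (seven parameters), one parameter each for treatment, mutation type, age, sex, smoking and ECOG PS (an assumption) gives 13. Events per parameter then go from 144/13 ≈ 11 to 144/15 ≈ 10.

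Leave the allocation factors as they are. By 23 December 2021, 58 patients had been enrolled, and altering a live dynamic system across eight blinded centers is not clearly cheap for a factor the model already covers. This fix does not touch the log-rank test, which stays unstratified.

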## Abstract

**Background:** Epidermal growth factor receptor (EGFR) tyrosine kinase inhibitors (EGFR-TKIs) significantly improve the prognosis of non-small cell lung cancer (NSCLC) with EGFR mutation-positive. Although third-generation EGFR-TKI osimertinib is demonstrated with superior efficacy compared with first-generation EGFR-TKIs, acquired resistance to EGFR-TKIs remains the bottleneck. The Chinese herbal medicine (CHM) Yiqi-Yangyin-Jiedu decoction (YYJD) has been shown to delay acquired resistance to first-generation EGFR-TKIs in the CATLA study, but there is no high-level evidence for its effect when combined with osimertinib. This trial aims to evaluate the efficacy and safety of YYJD combined with osimertinib as first-line treatment in EGFR mutation-positive advanced NSCLC.

**Methods:** This is a double-blind, multi-center, randomized controlled trial conducted in eight hospitals in China. A total of 314 participants will be randomly assigned to the osimertinib plus YYJD group (O+YYJD) or the osimertinib plus placebo group (O+placebo). Treatment will last until disease progression or death. Patients diagnosed with advanced NSCLC harboring EGFR Ex19del or L858R will be enrolled if they are ready to take osimertinib as first-line treatment, aged 18–74 years old, and provide signed informed consent. The primary outcome is progression-free survival (PFS). The secondary outcomes include a comparison of overall survival (OS), objective response rate (ORR), disease control rate (DCR), and quality of life (QoL). The analysis will be based on intention-to-treat and per-protocol subject analysis principles.

**Discussion:** The goal of this trial is to evaluate the efficacy and safety of YYJD when added to osimertinib as first-line treatment in EGFR mutation-positive advanced NSCLC.

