#### Osimertinib

Osimertinib (TAGRISSO, AstraZeneca, United Kingdom) should be taken at 80 mg per day. Patients enrolled in this study should continue intervention until disease progression or intolerable adverse effects.

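### Adverse events are tested as crude frequencies although time at risk ends at progression, which tilts the comparison modestly against YYJD if it works as planned

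*Protocol article*

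**What the plan says.** All statements come from the protocol article.

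- **Test (Statistical Analysis).** "The frequency difference of adverse events between groups will be assessed by the chi-square test" or Fisher's exact test. Severity grades are also compared without reference to time: "For different AE severities, a rank-sum test will be performed to analyze the independent ordered multiple category data between the two groups". The section sets two-sided significance at 0.05. The safety set is everyone who received at least one treatment after randomization.
- **AE window (Secondary Outcomes, item 6).** "all adverse events (AEs) during treatment will be recorded at each visit, and all AEs reported will be analyzed".
- **Length of treatment.** The Abstract has "Treatment will last until disease progression or death". The Osimertinib section has "Patients enrolled in this study should continue intervention until disease progression or intolerable adverse effects". Under Study Design, visits follow the same pattern: "Follow-up will be conducted at baseline, 4 weeks after treatment, and every 8 weeks afterward until disease progression or death".
- **Expected difference (Sample Size).** Median progression-free survival (PFS) is 18 months for control and 23 for YYJD, with 18 months of recruitment, 30 months in total, 1% monthly censoring and 157 patients per arm.

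No section mentions patient-time, exposure-adjusted rates, time to first AE or a fixed AE window. Under Drop-Out Criteria, safety evaluation continues after a patient drops out, for a period that is not given.

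**The concern.** The period over which AEs are counted ends mainly at progression, the event that YYJD is meant to postpone. A chi-square or Fisher test on the proportion of patients with an AE treats the two arms as observed for equal time. If YYJD delays progression, its patients stay in the counting window longer and more of them will have an AE even when the rate per month is the same. If YYJD shortened treatment, the tilt would run in its favour.

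The Discussion considers it reasonable to speculate that YYJD may lower the toxicity of osimertinib, and the Abstract names safety beside efficacy as the aim. The planned test works against seeing lower toxicity precisely when the primary endpoint goes well.

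**Working it through.** The plan gives no AE rate, so there is no stated AE figure to reproduce. The check asks how far two arms with the **same** AE hazard would differ on the crude measure.

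**Inputs from Sample Size.** Medians 18 and 23 months; uniform recruitment over 18 of 30 months, so potential follow-up runs evenly from 12 to 30 months; 1% monthly censoring; 157 per arm.

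**Assumptions added here.** Exponential PFS and censoring; treatment ends at progression or death, censoring or month 30; constant AE hazard h of 1%, 3% or 6% per month; all 157 per arm in the safety set. Stopping for intolerable adverse effects is not modelled.

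**Step 1: rate of leaving treatment**, k = ln 2/median − ln 0.99
- Control: 0.03851 + 0.01005 = 0.04856 per month
- YYJD: 0.03014 + 0.01005 = 0.04019 per month

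**Step 2: mean time on treatment to month 30**, E = (1/k)·[1 − (e^(−12k) − e^(−30k))/(18k)]
- Control: (1 − 0.3254/0.8741)/0.04856 = 12.93 months
- YYJD: (1 − 0.3179/0.7234)/0.04019 = 13.95 months
- Ratio: 13.95/12.93 = 1.079

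**Step 3: proportion with at least one AE.** With K = k + h, p = (h/K)·[1 − (e^(−12K) − e^(−30K))/(18K)]. For h = 0.06:
- Control: (0.06/0.10856)·(1 − 0.2333/1.9541) = 48.7%
- YYJD: (0.06/0.10019)·(1 − 0.2510/1.8034) = 51.6% (51.55% before rounding)

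**Step 4: size of the nominal 5% test.** With d the difference and SE its standard error at 157 per arm, the rejection rate is approximately Φ(d/SE − 1.96) + Φ(−d/SE − 1.96). For h = 0.06, d/SE = 2.88/5.64 = 0.51, giving 0.0735 + 0.0067 = 8.0%.

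| Assumed h per month | Control | YYJD | Excess (points) | SE (points) | Rejection rate |
|---|---|---|---|---|---|
| 1% | 11.8% | 12.7% | 0.9 | 3.7 | 5.7% |
| 3% | 30.2% | 32.3% | 2.1 | 5.2 | 6.8% |
| 6% | 48.7% | 51.6% | 2.9 | 5.6 | 8.0% |

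The true rate ratio per patient-month is 1.00 in every row.

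**Step 5: early onset.** Let the hazard act only in the first w months. All patients have at least 12 months of potential follow-up, so p = (h/K)·(1 − e^(−Kw)).
- w = 3, h = 0.266: 51.7% versus 52.3%, an excess of about 0.6 points
- w = 6, h = 0.133: 48.7% versus 49.7%, an excess of 1.0 point

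**Step 6: masking.** Set h so that control incidence is 50% (h = 0.0628) and give YYJD a hazard that is truly 10% lower. At equal exposure the crude figures would be 46.9% versus 50%. With the planned exposure they are 49.8% versus 50%. For a control incidence of 30%, 27.6% becomes 29.6%.

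**The case against.** **The unseen analysis plan may deal with this.** The article defers to a statistical analysis plan, and extra safety tables are often specified there. That stands for anything the article leaves open. But the article itself names the between-arm test, and that test ignores time at risk.

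**Crude incidence is conventional and answers a real question.** Patients treated longer do have those extra events, so the share affected over a course of treatment is a legitimate description. This stands, and is why the crude table should stay. The excess is spurious only when the test is read as evidence that YYJD changes the rate of AEs.

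**The shift is small.** At the planned medians it is 0.24 to 0.51 standard errors, and it depends on a constant hazard that the article does not support or exclude. This stands and limits the weight of the point.

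**Stronger readings that the article does not support:**
- A reader might infer a distortion of 5 points or more. An intervention median of 29.2 months with h = 6% would give 54.0% versus 48.7%, but that median appears nowhere in the article, which plans 23 months.
- A reader might take recording to stop strictly at progression. Treatment also ends for intolerable adverse effects, and safety evaluation continues after drop-out. Nothing stated, however, makes the window equal between arms.
- A reader might take the side effects listed in the Discussion as pre-specified osimertinib toxicities. They are findings from the earlier trial with gefitinib, erlotinib or icotinib.
- A reader might fear a false claim of safety. If YYJD delays progression, the tilt runs against it. Nor does the article fix a hypothesis of lower toxicity.

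**Conclusion.** The point holds at modest size. The article fixes a test of AE frequencies that disregards time at risk, while its own assumptions give the YYJD arm about 8% more treatment time to month 30. With equal constant hazards of 1% to 6% per month, the result is an excess of about 1 to 3 percentage points on YYJD and a test that rejects about 6% to 8% of the time instead of 5%. For AEs confined to the first 3 to 6 months, the excess is about 0.6 to 1 point.

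These sizes rest on exponential times and on assumed AE hazards, and they arise only if YYJD does delay progression. The practical consequence is that a moderate true reduction in toxicity could be partly or almost wholly hidden. This is a worthwhile improvement to the safety analysis, not a threat to the trial's primary conclusion.

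**What to change.** 1. Keep the crude incidence table by arm as description.
2. Base the between-arm comparison on exposure-adjusted incidence: first events divided by patient-months at risk up to the first event or the end of the AE window, with a rate ratio and 95% CI.
3. Add time to first AE, with progression or other treatment end and death handled as competing events. Use the cause-specific hazard ratio for the comparison and cumulative incidence curves for description. A test on the cumulative incidence itself would bring the exposure difference back in.
4. Fix the AE terms for these comparisons before unblinding. The side effects that the Discussion reports from the first-generation EGFR-TKI trial (fatigue, loss of appetite, diarrhea, pruritus, rash) are candidates.
5. State when the AE window closes, including for patients who drop out, so that the denominator is defined.

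**Cost.** Wording in the analysis plan and one extra table. The rate ratio assumes a roughly constant rate, which the time-to-first-AE analysis does not need. The article does not say that treatment start and stop dates are recorded, so their capture on the case report form must be confirmed.
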